**7. ETHICAL CONSIDERATIONS**

**7.1 Study Procedure Benefits**

This study should provide a direct benefit to the participant in the form of anorectal biofeedback therapy. Participants in all study groups should receive some level of therapy equal to or higher than what is currently available. The outcomes of this study will increase the clinical community’s understanding defecation disorders and anorectal physiology. Our findings may contribute towards the development of a novel approach to deliver BF therapy. Ultimately this may, lead to readily accessible treatment of defection disorders. Data from this study will be used as part of regulatory submission and possible commercialisation of this product in Australia. This outcome will enable the hospitals to provide this intervention after the completion of the project.

**7.2 Study Procedure Risks**

Potential risks associated with the novel home-based BF device are summarised in Table 2.

**Table 2.** Identified risks and mitigation activities

| Identified Risk | Probability | Impact | Mitigation Strategies |
| --- | --- | --- | --- |
| Bacterial and faecal contamination on probe | Occasional  (1 in 10K) | Minor | - Labelling: directions for use, single person use only - Condom sheath over probe for insertion - Wipe down with clean-wipes after use |
| Probe breaking during use | Remote  (1 in 100K) | Serious | - Bend testing of probe determined >5 kg of pressure required to compromise structural integrity (far above anorectal muscle forces). - Insertion and use in the lying position to avoid accidental slips and falls |
| Perform exercise incorrectly | Probably  (1 in 1K) | Negligible | - Training with therapist (first session) before home use - Software to detect incorrect placement or use, then instructs user to adjust or remove probe |
| Anal tearing/perforation | Remote  (1 in 100K) | Serious | - Exclude users with anal fissure and haemorrhoids - Use with lubricant - Immediate removal with any discomfort or pain |
| Electric shock | Remote  (1 in 100K) | Minor | - Power source (battery) is located in the base and external of the body during use - Labelling: not to be submerged in water - In-built moisture detection kill switch in circuit - Low voltage lithium battery (3.7 V; 700 mAh) |

Precautions have been taken to mitigate all risks but in the chance of an adverse event the participant can contact the lead investigator ([name]). [name] will ask the participant to stop using the device and discuss the severity of the incident with study clinicians ([name] or [name]) to best advise participant of their course of action (e.g. return the device for replacement, consultation with clinician, visit emergency department).

The recording and reporting of adverse events will be classified based on their severity (“Negligible”, “Minor”, “Serious”, “Critical”, and “Catastrophic”). All events classified as “minor” or above in severity will be recorded and notified to the Principle investigator ([name]) and site coordinating investigator ([name]). Events classified as “Serious” or above will be will reported to HREA in to form of a “safety report” and trial will be temporarily suspended to investigate cause of event and implement appropriate mitigation strategies (e.g. instructions-of-use, technical updates, update cleaning procedure).

The clinicians involved in this study ([name] and [name]) will be available to help if any adverse events or symptoms occurs during the study. They will be able to provide medical advice and determine the best course of action.

To avoid coercion or inducement, an investigator not directly involved in the participant’s treatment (e.g. [name]) will be explaining the procedure and obtaining informed consent.

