Group B participants will undergo 6 supervised clinic sessions with the experimental device. After session two, they may also take the device home and continue training during the treatment period. The wireless device contains sensors to measure anal sphincter and rectal pressures. A condom sheath is placed over the probe before it is inserted into the anal canal. The user will download the training program (mobile app) onto their mobile phones, which will guide the user through the required exercises (identical to the clinic-based BF manoeuvres listed above). Participants will be asked to insert the probe and perform training for 5 – 10 minutes daily over a training period of 2 months. Training data is send to a cloud server for therapist to monitor compliance and correct usage. The participants are asked to keep daily bowel and food diaries on the app, this information is sent to the cloud accessible only by the therapist and investigators.

Upon completion of the feasibility study, home-based BF with novel device at Site 2 (Group B) will only undergo one supervised training session with the novel device. Participants then take the device home and continue training unsupervised for the duration of their treatment period. The therapist monitor adhesion remotely through the cloud server and will arrange fortnightly telehealth consultations to provide encouragement and evaluate progress.

At the end of the treatment period, participants in Group B will undergo a short useability interview. The therapist will ask the participant questions regarding the 1. Ease of use, 2. Clarity of instructions, 3. Ease of cleaning, 4. Any additional Issues.

*Data analyses*

At the end of the treatment period participants will return to the clinic for a repeat anorectal manometry study to determine changes in anorectal physiology parameters. The therapist will also review their bowel and food diaries. The therapist will discuss the results with the participants and plan the next course of action.

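### No scheduled, identical adverse-event enquiry is specified in either arm and Negligible events need not be recorded, so harms data are open to under-capture and, at Site 2, to possible ascertainment bias

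*Protocol*

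**What the plan says.** Protocol Section 7.2 describes reporting by the participant: "in the chance of an adverse event the participant can contact the lead investigator". The lead investigator then "will ask the participant to stop using the device and discuss the severity of the incident with study clinicians". The study clinicians "will be available to help if any adverse events or symptoms occurs during the study".

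The same section sets the recording rule. "The recording and reporting of adverse events will be classified based on their severity", on a five-grade scale: Negligible, Minor, Serious, Critical, Catastrophic. "All events classified as “minor” or above in severity will be recorded and notified" to the responsible investigators. Events graded Serious or above also trigger a safety report and a temporary suspension of the trial.

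Section 5.8 describes the contacts. Group A attends at most six clinic sessions over 2 months, at which the therapist discusses progress and clinical indicators. At Site 1, Group B also has six supervised clinic sessions. At Site 2, Group B has one supervised session and then trains unsupervised at home, and the therapist "will arrange fortnightly telehealth consultations to provide encouragement and evaluate progress". Participants return for repeat manometry at the end of treatment, and Group B has a usability interview.

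Section 7.1 states the intended use: "Data from this study will be used as part of regulatory submission".

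**The concern.** Harms that participants must volunteer are usually recorded less completely than harms they are asked about, and completeness then depends on how often and in what setting each participant meets staff. At Site 2 that setting differs by arm by design. A threshold that leaves the lowest grade unrecorded removes further information, and an event that was never written down cannot be re-graded when its significance becomes clearer.

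Two things are at stake. First, the safety record offered to a regulator may be incomplete, and any contrast between arms drawn from it may partly reflect how events were found. Second, the suspension rule for Serious events can act only on events that are detected and graded.

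**Working it through.** The protocol gives no adverse-event rate, detection probability or safety sample size, so there is no stated figure to reproduce. The check is a reading of the relevant sections and a count of scheduled contacts.

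**1. Is any contact tied to an adverse-event enquiry?**

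| Contact (Protocol section) | Arm | Stated content | Adverse-event enquiry stated? |
| --- | --- | --- | --- |
| Clinic sessions (5.8) | A | Progress, clinical indicators | No |
| Telehealth calls (5.8) | B, Site 2 | Encouragement, progress | No |
| Bowel diary (5.3, 5.8) | Both | Bowel habits, stool consistency, symptoms | No |
| Remote monitoring of training data (5.8) | B | Compliance, correct usage | No |
| End-of-treatment visit (5.8) | Both | Repeat manometry, diary review | No |
| Usability interview (5.8) | B | Ease of use, instructions, cleaning, any further issues | No |

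Several of these could bring a harm to light. None is linked to adverse-event recording, and the one stated reporting route is the participant's own approach to the investigator.

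**2. What does the recording threshold leave out?** One of the five grades, Negligible, has no recording requirement. In Table 2 of Section 7.2 the hazard with the highest stated probability, performing the exercise incorrectly (1 in 1K), carries that impact rating. The same table lists removing the probe on any discomfort or pain as mitigation for anal tearing, which is rated Serious. The table thus treats discomfort as a reason to act, but discomfort graded Negligible need not be recorded. No arm is named in the threshold, so it applies to both.

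**3. How does scheduled contact compare by arm?** Taking 2 months as 8 to 9 weeks, fortnightly calls number about 8/2 = 4.

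- Site 2, in person: Group A up to 6 sessions + 1 end visit = up to 7; Group B 1 session + 1 end visit = 2.
- Site 2, all scheduled contacts: Group A up to 7; Group B 1 + about 4 + 1 = about 6.
- Site 1: up to six clinic sessions in each arm plus the end visit, so no imbalance in scheduled contact.

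The Site 2 arms therefore differ clearly in face-to-face contact and little in total contact.

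**4. Can the effect be sized?** No. That would need the event rate per arm and the probability that an event is reported at each kind of contact, and the document gives neither.

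**The case against.** A reader might infer that events are captured solely when a participant makes contact. The protocol does not say so. The symptom diary, telehealth calls, remote monitoring, end visit and usability interview are all places where harm could surface. This objection stands. What remains is that the protocol links none of them to adverse-event recording.

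A reader might also infer that harms in home users will be under-counted relative to clinic patients. The documents do not support that direction. Group A sessions are no more described as adverse-event enquiries than the telehealth calls are. Total scheduled contacts at Site 2 are similar. The usability interview is given to Group B alone, and the response in Section 7.2 is written around stopping the device, with no parallel text for manometry. Both features could raise capture in Group B. The Negligible threshold applies to both arms, so by itself it lowers counts without creating a difference between them.

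It is tempting to attach a number by assuming that some fraction of events is reported. Any such figure would come entirely from the assumption and would say nothing about a difference between arms, so none is given here.

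Finally, neither the outcomes in Section 3 nor the analyses in Section 5.8 include a safety outcome or a between-arm comparison of harms. That limits the consequence: no planned test is invalidated. It does not remove the point, because Section 7.1 commits the data to a regulatory submission. How events are elicited and recorded is also a matter of trial conduct that Section 7.2 already fixes, so it is not a detail left to the SAP.

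**Conclusion.** The point holds in limited form. As written, the protocol relies on participant-initiated reporting, specifies no common schedule of adverse-event questions in either arm, and does not require the lowest severity grade to be recorded. Harms data can therefore be incomplete in both arms. At Site 2, where in-person contact is up to 7 v 2, completeness may also differ between arms.

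Neither the direction nor the size of any difference can be determined from the document. The contact counts assume a treatment period of 8 to 9 weeks, the maximum number of Group A sessions, and telehealth calls held as planned. The conclusion also assumes that no separate safety procedure or case report form, not shown here, already prescribes the questions. This is a worthwhile and inexpensive improvement; it is not a flaw in the efficacy comparison.

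**What to change.** In Sections 5.8 and 7.2, add three provisions:

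- Ask the same short, fixed list of adverse-event questions in both arms at contacts that already exist: each clinic session, each fortnightly telehealth call and the end-of-treatment visit.
- Record every event with its date, arm and grade, including Negligible.
- Keep Minor or above as the threshold for notifying the investigators, and no longer as the threshold for recording.

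No visit is added, and the reporting and suspension rules for Serious events are untouched. The cost is one form, a few minutes per contact and more low-grade events to tabulate. Clinic sessions and telehealth calls will not match exactly in number or setting, so recording the contact at which each event was elicited would let readers judge any remaining imbalance.

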**7.2.1 COVID-19 Considerations**

The in-person consultation and BF training carry a low risk of aerosolisation of virus particles and transmission to the staff. The study will follow general contact and droplet precautions detailed in the advice from: https://www.cec.health.nsw.gov.au/keep-patients-safe/COVID-19. Investigator will provide their own protective personal protective wear (gloves and mask), which will be wore when approaching participants and instructing the procedure. Investigators will also practice social distancing and maintain a 1.5m distance when conversing with participants. Participants will be asked if they experience COVID-19/flu-like symptoms, in the case of a positive symptoms, they would not be asked to take part in this study. The home-based devices are single person use and does not pose a risk of cross transmission of virus particles between participants. The room and equipment (bed, table, handles etc.) will be thoroughly cleaned with disinfectant between participants.

**7.3 Confidentiality and Privacy**

Identifiable participant information will remain on site on the Hospital’s password protected computer. Identifiable information (name, MRN, date of birth) will be kept on a “decoding sheet” in a separate folder to study data, only the PI will have access to the decoding sheet. De-identified health data will be stored on the site network using a data management software (RedCap).

Data collected by the device and app will be sent to a secure cloud server managed internally by Western Sydney University and only accessible by study investigators. This data used entered into RedCap in a non-identifiable form for analysis by investigators. Dissemination of data will in the form of descriptive statistics (e.g. mean±SD) in results and publications.

**7.4 Data storage and Record retention**

The information collected on paper copies of participant information will be physically locked up in a cabinet located in the offices of the study sites. Furthermore, identifiable electronic records will remain on the Hospital network folders. Device and app training data are stored on the secure Western Sydney University cloud server and the password is only accessible by the coordinating investigators and therapists.

A copy of the non-identifiable data for analysis will also be stored in RedCap a password protected computer within a locked office (30.2.65) at the School of Medicine, University of Western Sydney. As such only the investigators will have access to this information. The storage of data and information will be closely monitored by the principal investigators. If the confidentiality of participants is violated it will be immediately reported to a central monitoring committee. The information collected will be retained for 15 years per Section 2.3 Australian Code for the Responsible Conduct of Research. At the end of these 15 years paper copies will be shredded and appropriately disposed while electronic data will be deleted.

**8. CONFLICT OF INTEREST**

All investigators declare no financial interest or benefit that may arise from the direct applications of this research.

The investigators [name] and [name] are inventors of the experimental device and Western Sydney University is the owners of the intellectual property (IP). The inventors and Western Sydney University may have a financial interest in the device if it was commercialised

**9. FUNDING**

This project is funded by a research grant from SPHERE (Maridulu Budyari Gumal) Frontiers Technology and Translational Gastroenterology Laboratory at School of Medicine, Western Sydney University.

**10. RESEARCH OUTCOMES**

The proposed research outcomes will contribute towards our understanding of BF therapy and anorectal physiological. The broader impact of our findings may lead to improvements in the delivery of BF therapy though a home-based device that provides instrumented BF therapy equivalent to clinic-based BF.

The results of this study will be disseminated at national and international conferences along with relevant journals (such as The American Journal of Gastroenterology). The results of the individual studies will be available each participant (if they are interested) and provide as a lay report. The investigators aim to publish the results in an open access journal so that participants and the public would be able to readily access the outcomes of this study.

